## Abstract

**Background:**

Patients with end-stage kidney disease require complex and expensive medical management. Kidney transplantation remains the treatment of choice for end-stage kidney disease and is considered superior to all other modalities of renal replacement therapy or dialysis. However, access to kidney transplant is limited by critical supply and demand, making it extremely important to ensure longevity of transplanted kidneys. This is prevented through lifelong immunosuppression, with caution not to overly suppress the immune system, resulting in toxicity and harm. Transition of care to community nephrologists after initial kidney transplantation and monitoring at a transplant center is an important process to ensure delivery of effective and patient-centric care closer to home. Once transplanted, laborious surveillance of the immune system and monitoring for potential rejection and injury are undertaken through an armamentarium of screening modalities. Posttransplant surveillance for kidney function and injury remains key to follow-up care. While kidney function, quantified by estimated glomerular filtration rate and serum creatinine, and kidney injury, measured by proteinuria and hematuria, are standard biomarkers used to monitor injury and rejection posttransplant, they have recently been demonstrated to be inferior in performance to that of AlloSure (CareDx Inc, Brisbane, CA) circulating donor-derived, cell-free DNA (dd-cfDNA).

**Objective:**

The outcomes and methods of monitoring renal transplant recipients posttransplant have remained stagnant over the past 15 years. The aim of this study is to consider intensive surveillance using AlloSure dd-cfDNA in an actively managed protocol, assessing whether it increases long-term allograft survival in kidney transplant recipients compared with current standard clinical care in community nephrology.

**Methods:**

The study protocol will acquire data from a phase IV observational trial to assess a cohort of renal transplant patients managed using AlloSure dd-cfDNA and patient care managers versus 1000 propensity-matched historic controls using United Network for Organ Sharing U.S. Scientific Registry of Transplant Recipients data. Data will be managed in a centralized electronic data server. The primary outcome will be superior allograft survival, as a composite of return to dialysis, retransplant, death due to allograft failure, and death with a functional graft (infection, malignancy, and cardiovascular death). The secondary endpoints will assess improved kidney function through decline in estimated glomerular filtration rate and immune activity through development of donor-specific antibodies.

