Death with a functioning graft (DWFG) accounts for 47% of all transplant losses after 10 years. Additionally, registry data and retrospective analyses of long-term outcomes from randomized trials have highlighted cardiovascular disease, followed by malignancy as the top causes of morbidity and DWFG. However, while death from cardiovascular disease in RTRs appears to be declining, mortality from malignancy is increasing [17].

The increasing number of transplants worldwide is further resulting in a growing cohort of posttransplant recipients (179,361 RTRs in the United States in 2010); due to the limited number of transplant nephrologists, these patients are increasingly likely to encounter practitioners in other specialties. Thus, understanding the value of AlloSure dd-cfDNA in the context of long-term management is an area of key importance. The aim of this study is to assess the value of AlloSure dd-cfDNA and an actively managed protocol in the context of chronic complications and determine how it may influence long-term outcomes relevant to generalists.

As the number of kidney transplants performed continues to increase in the United States, so does the cohort of long-term RTRs, which was estimated at over 220,000 in 2017 [18]. With limited transplant nephrologists and hospital outpatient resources, many of these patients will be managed under a shared care model between community physicians and transplant centers. The Transition of Renal patients using AlloSure into Community Kidney care (TRACK) study aims to assess the utility of AlloSure dd-cfDNA surveillance and supplemental patient care management for RTRs in prolonging allograft survival and improving long-term clinical outcomes including graft function and immunological status.

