## Methods

### Study Design

This is a phase IV, prospective, multicenter, observational, cohort study designed to evaluate the effectiveness of AlloSure dd-cfDNA (CareDx Inc, Brisbane, CA) surveillance and patient care management in kidney transplant patients in prolonging allograft survival, allograft function, and immunological status. All prospective data will be collected from patient electronic medical records. Propensity-matched control data will be sourced from United Network for Organ Sharing U.S. Scientific Registry of Transplant Recipients databases. The study duration will be event driven, with each patient’s enrollment lasting 5 years.

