### Outcomes and Measures

The primary endpoint of this study will be superior graft survival measured as the time to allograft loss, defined as the composite of return to dialysis, retransplant, death due to allograft failure, and DWFG (infection, malignancy, and cardiovascular death).

Secondary endpoints include assessment of allograft function and immunological status. Allograft function will be measured as the relative change in eGFR from baseline between the 2 study groups: dd-cfDNA surveillance compared to controls. Immunological status will be defined by detection of de novo DSA formation in patients monitored using dd-cfDNA compared to the matched controls.

All clinical events and investigation results will be captured through the patient electronic medical record or via AlloCare, an optional smartphone-based application that provides a patient-driven platform to manage medications, access results, monitor wellness activities, and streamline communication with their care team. Patients will also be offered mobile phlebotomy when they are unable to visit a local laboratory. The mobile blood draw will be coordinated by CareDx, which will draw all regular tests, urine samples, as well as the AlloSure. Support for testing adherence will be provided by PCMs (CareDx Inc, Brisbane, CA) to assist with scheduling both in-center and mobile draws and provide laboratory visit reminders.

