**Exclusion Criteria**
Participant who is pregnant, lactating, or planning pregnancy during the trialSignificant hepatic impairment (determined by the principal investigator)Participant with life expectancy of <6 months or inappropriate for diagnostic monitoring through regular blood sampling<6 months and >18 months posttransplantAny other significant disease or disorder which, in the opinion of the investigator, may either put the participants at risk because of participation in the trial or may influence the result of the trial or the participant’s ability to participate in the trialParticipants who have participated in another research trial involving an investigational product in the past 12 weeksRecipients of multiorgan transplant (eg, kidney-pancreas)Recipients of a transplant from a monozygotic (identical) twinRecipients of nonautologous bone marrow transplantPatients with a history of poor compliance or needle phobia

A 2-sided log-rank test with an overall sample size of 3500 kidney transplant patients (of which 2500 will be periodically assessed with AlloSure and 1000 are matched controls receiving standard of care) achieves 87% power at a 5% significance level to detect an allograft survival difference of 5% (ie, 75%, AlloSure assessed; 70%, standard of care) during the 5-year surveillance period. This corresponds to a hazard ratio of 0.807, which is a 19.3% reduction in the risk of allograft loss in the AlloSure-assessed patients in comparison to standard of care. There is no consideration of patients lost to follow-up due to the United Network for Organ Sharing U.S. Scientific Registry of Transplant Recipients database, which tracks transplanted organ survival for all organ transplant recipients; however, this analysis does account for an attrition rate of 65%.

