## Results

This study received Western Internal Review Board approval in September 2020. A total of 20 community nephrology practices are expected to participate in this study. Active enrollment began in November 2020. Study insights and conclusions are expected to be presented intermittently throughout the study at international conferences and manuscripts submitted to peer-reviewed academic journals.

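### The abstract specifies historic registry controls for a comparison with current care; to the extent that the control era is earlier, calendar time cannot be separated from AlloSure

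*Protocol article*

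**What the plan says.** The abstract's Methods paragraph sets the AlloSure cohort against "1000 propensity-matched historic controls using United Network for Organ Sharing U.S. Scientific Registry of Transplant Recipients data". The abstract's Objective states the question as whether intensive surveillance improves graft survival "compared with current standard clinical care in community nephrology".

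Study Design repeats the source but not the word historic: "Propensity-matched control data will be sourced from United Network for Organ Sharing U.S. Scientific Registry of Transplant Recipients databases". It gives no transplant years, index date or follow-up dates for the controls. The same section says "The study duration will be event driven, with each patient’s enrollment lasting 5 years", and Results says "Active enrollment began in November 2020". The sample-size paragraph after the exclusion criteria describes the registry as one "which tracks transplanted organ survival for all organ transplant recipients".

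Outcomes and Measures makes the primary endpoint time to allograft loss, "defined as the composite of return to dialysis, retransplant, death due to allograft failure, and DWFG (infection, malignancy, and cardiovascular death". Two statements bear on time trends. The Objective says that outcomes and monitoring methods have not moved in 15 years. The Introduction says that "while death from cardiovascular disease in RTRs appears to be declining, mortality from malignancy is increasing".

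**The concern.** A patient in the AlloSure group is at risk from late 2020 onwards. A historic control is, on the ordinary meaning of the word, someone whose follow-up lay earlier. If that is what is done, group and calendar period move together. A propensity score built on patient characteristics can balance age, donor type or sensitisation. It cannot balance era where the groups do not share one. Any change between the periods in background mortality, immunosuppression or general care would then be read as an effect of AlloSure, or would mask one.

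The primary composite counts deaths with a functioning graft, and the Introduction puts these at 47% of losses after 10 years. Trends in causes of death therefore feed straight into the endpoint. The planned difference is only 5 percentage points in 5-year survival, so a modest shift in the background is large relative to the target. Controls from an earlier era would also not represent the current care named in the objective.

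**Working it through.** **Inputs from the sample-size paragraph.** 2500 AlloSure and 1000 controls (AlloSure fraction a = 2500/3500 = 0.714); 5-year graft survival 75% and 70%; two-sided 5% log-rank test; stated power 87%; stated attrition 65%. **Assumed, because the document gives no figure:** the size and direction of the time trend, and a 5-year gap between eras.

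**1. The plan's own figure.** HR = ln(0.75)/ln(0.70) = 0.8066, against 0.807 stated. Events without attrition = 2500 × 0.25 + 1000 × 0.30 = 925. Freedman's formula with k = 2.5 gives z = √(925 × 2.5) × (1 − 0.8066)/(1 + 2.5 × 0.8066) = 48.09 × 0.1934/3.016 = 3.08. Power = Φ(3.08 − 1.96) = 0.87. The 87% reproduces, but without attrition. Schoenfeld's formula gives 0.84 on the same inputs and is used below.

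**2. Critical value.** With 925 events, an observed HR at or below exp(−1.96/√(925 × 0.714 × 0.286)) = 0.867 is significant in favour of AlloSure.

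**3. Falling background hazard, no AlloSure effect.** The apparent HR is (1 − annual fall)^5. Survival in the AlloSure group is 0.70^HR. Events = 2500 × (1 − that survival) + 300. The chance of a significant result for AlloSure is Φ(√(events × a × (1 − a)) × (−ln HR) − 1.96).

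| Annual fall | Apparent HR | Events | False superiority, no attrition | Events × 0.35 | False superiority, scaled |
|---|---|---|---|---|---|
| 1% | 0.951 | 1019 | 11% | 357 | 6% |
| 2% | 0.904 | 989 | 30% | 346 | 13% |
| 3% | 0.859 | 960 | 57% | 336 | 24% |

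The nominal rate in this direction is 2.5%. Scaling all events by 0.35 is the crudest reading of 65% attrition. If only the AlloSure group is cut by 65%, because the registry follows the controls, the figures are about 9%, 22% and 42%. With a 3-year gap and no attrition they are 6%, 14% and 26%.

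**4. The same in survival terms, no attrition.** If background 5-year survival rose from 70% to 72% with no AlloSure effect, false superiority is about 22%. A rise to 75% equals the whole target effect, and false superiority is about 84%.

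**5. Rising background hazard, true HR 0.8066, no attrition.**
- A 5% rise gives an apparent HR of 0.8066 × 1.05 = 0.847 and power of 64%.
- A 10% rise gives 0.8066 × 1.10 = 0.887 and power of 39%.
- With no rise, power is 84%.

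**6. The two statements on trends.** The Objective's claim of 15 unchanged years would, if true of the composite, make the control era unimportant. The Introduction reports movement in two of the composite's named causes of death. The trends run in opposite directions and neither has a size, so the text fixes neither the sign nor the size of the net shift.

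**The case against.** The strongest reply is that non-overlap is inferred. The word historic appears once, in the abstract. Elsewhere the controls are only called matched or propensity-matched, and no control years are given. This is a condensed article, and the matching variables and control period may well stand in the full protocol. The first AlloSure patients were themselves transplanted 6 to 18 months before their first draw, so a control era ending shortly before theirs would leave only a small gap. If the eras partly overlap, transplant year can be matched or adjusted for. All of this stands. A reader might infer that the two groups share no calendar time at all; the document does not establish that.

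A reader might also infer that the comparison is biased in favour of AlloSure. That is not supported either. The authors state their reason for treating past care as representative, namely that outcomes have been flat. The Introduction qualifies that premise, but with two opposing trends that may partly cancel. No figure in the document supports a net fall of 1% to 3% a year.

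Finally, historic controls have a real advantage: they are less likely to have had dd-cfDNA testing. Contemporaneous controls may receive it, and nothing in the document says that the registry records it.

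What remains is that historic is a stated design choice, not an omitted detail. Nothing in the body withdraws it, and it sits badly with an objective about current care.

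**Conclusion.** The point holds conditionally. As the abstract is written, the comparator does not match the objective. To the extent that controls come from an earlier era, the primary test cannot tell AlloSure from calendar time. The direction of any bias is undetermined, and its size cannot be derived from the document.

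The percentages above are illustrations that rest on an assumed trend, an assumed 5-year gap, the Schoenfeld approximation and the stated or assumed attrition. They show that a test aimed at a 5-point difference is sensitive to modest drift. False superiority could run from about 6% to 57% across the 5-year scenarios shown, or power could fall to between 39% and 64% if the background worsened by 5% to 10%. The sponsor should change this, because the named source covers all recipients and the exposure to drift is largely avoidable. If contemporaneous controls were always intended, the word historic is wrong and should be corrected.

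**What to change.** Replace historic by contemporaneous, and state the control period. Draw controls from registry recipients transplanted in the same calendar period as the AlloSure cohort. Match them on transplant date, index them at the same time since transplant (within the 6 to 18 month window) and follow them over the same dates. If earlier-era controls are kept, use them only in a sensitivity analysis.

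The cost is a different extract from the same source. The AlloSure group needs its 5 years of follow-up in any case, so the main analysis need not wait longer, apart from any registry reporting lag, on which the document is silent. The downside is that some contemporaneous controls may receive dd-cfDNA testing, which dilutes the effect; the document gives no basis for sizing this. Where testing data can be obtained, exclude only controls tested before index, and report later testing as contamination rather than excluding on it. Where such data cannot be obtained, state this as a limitation.

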**Results:**

The total sample is anticipated to be 3500 (2500 patients managed with AlloSure dd-cfDNA and 1000 propensity-matched controls). Active enrollment began in November 2020.

**Conclusions:**

Based on a significant literature base, we believe implementing the surveillance of dd-cfDNA in the kidney transplant population will have a positive impact on graft survival. Through early identification of rejection and facilitating timely intervention, prolongation of allograft survival versus those not managed by dd-cfDNA surveillance protocol should be superior.

**International Registered Report Identifier (IRRID):**

PRR1-10.2196/25941

## Introduction

The recent presidential executive order to advance American kidney health has directed the U.S. Department of Health and Human Services to increase the number of patients with new end-stage kidney disease (ESKD) to either receive dialysis at home or receive a transplant, with the aim to double the number of kidneys transplanted by 2030 [1].

With over 700,000 patients living with ESKD in the United States, ensuring allograft longevity post-kidney transplant is critical [2]. As compared with dialysis, kidney transplantation is known to provide superior quality of life, patient survival, and cost-effectiveness [3-6].

Minimally invasive biomarkers to detect allograft injury and rejection have become increasingly important as clinicians strive to develop new strategies for personalization of medicine and prolonging allograft survival. Since its discovery in 1948, cell-free DNA has had a significant impact on molecular diagnostics and is now utilized frequently in prenatal genetic screening, preclinical neoplasia detection, and more recently, solid organ transplantation [7]. In recent years, donor-derived, cell-free DNA (dd-cfDNA) has shown clinical validity as a leading biomarker of allograft inflammation and injury [8-11].

In the Circulating Donor-Derived Cell-Free DNA in blood for diagnosing Acute Rejections in Kidney Transplant Recipients (DART) study, Bloom et al [8] assessed 102 paired renal allograft biopsies with dd-cfDNA. The median levels of dd-cfDNA in patients with a histological diagnosis of active rejection were significantly elevated compared to those without active rejection (1.6% versus 0.3%, *P*<.01). The receiver-operating characteristic area under the curve was reported at 0.74, which significantly outperformed serum creatinine at 0.54 in detecting active rejection. The performance characteristics of this assay were improved when discriminating antibody-mediated rejection (ABMR) from no ABMR, with an area under the curve of 0.87 [8]. Huang et al [10] validated these findings in a single-center study assessing 63 highly sensitized renal transplant patients with paired allograft biopsies and AlloSure dd-cfDNA.

More recently, in the Resolution by AlloSure Differentiates Ambiguous Rejection (RADAR) study, Stites et al found that AlloSure dd-cfDNA >0.5% can aid in the risk stratification of patients with T-cell mediated rejection grade 1A or borderline rejection with respect to poor clinical outcomes identified as estimated glomerular filtration rate (eGFR) decline, de novo donor-specific antibody (DSA) formation, and recurrent rejection episodes [11].

AlloSure dd-cfDNA has also shown associations with de novo DSA formation and ABMR previous to RADAR. Jordan et al [12] identified 90 dd-cfDNA samples paired with DSAs and clinically indicated biopsies and demonstrated the combination of dd-cfDNA and DSA testing improved the diagnostic yield of noninvasive diagnosis of ABMR to 89% positive predictive value.

Understanding the severity of opportunistic infections in immune-suppressed patients resulting in kidney injury is another area of utility. dd-cfDNA has been demonstrated to aid in differentiation of BK viremia and BK nephropathy, as well as help in cases with high viral copy number and confounding biopsy results [13,14].

Further, it is estimated that 60% of late rejections and 30% of early rejections can be attributed to posttransplant nonadherence to immunosuppressants. A meta-analysis and systemic review demonstrated patients who receive adherence intervention have significantly higher compliance (odds ratio=2.366) [15]. Transplant centers currently utilizing patient care managers (PCMs) also have improvements in patient adherence, upwards of 30% (unpublished data). These findings, in conjunction with other supporting evidence, demonstrate that the analysis of dd-cfDNA and PCM support are helpful in the assessment of transplant patients and provide additional information of allograft status.

In addition to allograft rejection, the clinical significance of other morbidity-affecting outcomes remains significant. Malignancy, infection, cardiovascular complications, and bone complications are an inevitable consequence of a lifetime of immunosuppression, adding a significant burden on patients and the health care system. Management of these patients is complex and often multidisciplinary, where AlloSure can provide additional, previously lacking, information about the allograft. This was recently demonstrated in a case report by Lipson et al [16] in the management of a renal transplant recipient (RTR) on checkpoint inhibitors to treat malignancy.

Death with a functioning graft (DWFG) accounts for 47% of all transplant losses after 10 years. Additionally, registry data and retrospective analyses of long-term outcomes from randomized trials have highlighted cardiovascular disease, followed by malignancy as the top causes of morbidity and DWFG. However, while death from cardiovascular disease in RTRs appears to be declining, mortality from malignancy is increasing [17].

The increasing number of transplants worldwide is further resulting in a growing cohort of posttransplant recipients (179,361 RTRs in the United States in 2010); due to the limited number of transplant nephrologists, these patients are increasingly likely to encounter practitioners in other specialties. Thus, understanding the value of AlloSure dd-cfDNA in the context of long-term management is an area of key importance. The aim of this study is to assess the value of AlloSure dd-cfDNA and an actively managed protocol in the context of chronic complications and determine how it may influence long-term outcomes relevant to generalists.

As the number of kidney transplants performed continues to increase in the United States, so does the cohort of long-term RTRs, which was estimated at over 220,000 in 2017 [18]. With limited transplant nephrologists and hospital outpatient resources, many of these patients will be managed under a shared care model between community physicians and transplant centers. The Transition of Renal patients using AlloSure into Community Kidney care (TRACK) study aims to assess the utility of AlloSure dd-cfDNA surveillance and supplemental patient care management for RTRs in prolonging allograft survival and improving long-term clinical outcomes including graft function and immunological status.

